# Mobile Phone–Based Smoking-Cessation Intervention for Patients Undergoing Elective Surgery: Protocol for a Randomized Controlled Trial

**DOI:** 10.2196/12511

**Published:** 2019-03-26

**Keywords:** smoking cessation, mobile phone–based interventions, SMS, mHealth interventions

## Abstract

**Background:**

Several large studies have shown that the risk of cardiovascular, respiratory, and wound-healing complications (including death) within 30 days of surgery is greater for smokers than for nonsmokers. However, there is evidence that even short-term perioperative smoking cessation may reduce postoperative morbidity. Over the past few years, it has become more evident that short message service (SMS)–based interventions can help individuals quit smoking.

**Objective:**

The overall aim of this project is to fill the knowledge gap on whether an SMS-based smoking-cessation intervention can be effective in helping patients stop smoking perioperatively. The aim of this trial is to evaluate the effectiveness of an SMS-based intervention on smoking behavior of patients undergoing elective surgery.

**Methods:**

A two-arm parallel-group randomized controlled trial will be conducted at 20 surgical departments in southeast Sweden. Smokers undergoing elective surgery who own a mobile phone will be included. Power calculations indicate that it will be necessary to randomize 434 participants. One group will be given access to a novel 12-week SMS program, which includes daily SMS messages with behavior change–enforcing text content and hyperlinks to interactive modules, while the other group will not be given access to the intervention. Both groups will have access to the surgical departments’ current routine for smoking cessation prior to surgery. Primary outcome measures, prolonged abstinence, and point prevalence of smoking cessation will be measured through questionnaires at 3, 6, and 12 months after randomization. Logistic regression models adjusted using baseline characteristics will be explored to identify potential effects of the intervention.

**Results:**

Recruitment started in late October 2018 and is expected to last for a maximum of 30 months. The first results are expected to be available approximately 3 months after the final date of recruitment.

**Conclusions:**

Owing to the structural problems and scarcity of time and resources, patients at most Swedish surgical departments are simply instructed to quit smoking, and perhaps, referred to a primary health care clinic. An SMS-based smoking-cessation aid can be effective in helping individuals quit smoking and is a very simple and time-efficient tool for surgical departments to use.

**Trial Registration:**

ISRCTN Registry ISRCTN33869008; http://www.isrctn.com/ISRCTN33869008

**International Registered Report Identifier (IRRID):**

PRR1-10.2196/12511

## Introduction

### Background and Rationale

Smoking is responsible for more than 60 diseases and is the single most influential preventable factor for disease and premature mortality [1]. In Sweden, tobacco is associated with 9.6% of the total disease burden [2]. Around 6400 people die every year in Sweden due to smoking. The previously recorded decline in the number of smokers in Sweden has started to level out, and in 2016, the proportion of smokers among both women and men was 9% [3]. Among individuals aged 45-64 years, the proportion of daily smokers was higher than that for any other age group—13% for women and 9% for men. Including occasional smokers, these proportions increase to 16% for women and 13% for men [3].

Studies show that approximately 65% of all smokers want to quit, and approximately 50% make at least one quit attempt each year, but only 10% seek or gain access to evidence-based supportive measures [4]. In addition to the addictive nature of smoking, the cost of treatment and time commitment make cessation a challenge [5,6].

Over 70 years ago, The Lancet published an article describing increased surgical complications after operation for patients who were smokers [7]. Since then, several large studies have shown that the risk of cardiovascular, respiratory, and wound-healing complications (including death) within 30 days of surgery is greater for smokers than for nonsmokers [8,9]. However, there is evidence that even short-term perioperative smoking cessation may reduce postoperative morbidity [5,10].

The rationale behind smoking cessation before surgery is that the short-term harmful effects of carbon monoxide and nicotine in the blood disappear 24-48 hours after smoking cessation. The harmful effects of carbon monoxide are mediated by a reduction in the availability of oxygen to the tissues by 3%-12% and associated with an increased risk of cardiac arrhythmias [10]. Nicotine stimulates the surgical stress response and increases the blood pressure, pulse rate, and systemic vascular resistance, thereby increasing the workload of the heart [10]. As anesthesia and surgery cause an increased strain on cardiac and circulatory functions, an existing oxygen imbalance can be worsened in patients who smoke, potentially resulting in hypoxemia in vital organs. Smoking also induces mucus production, which might impede the clearance of mucus, leading to an increased risk of postoperative pulmonary infections in combination with a reduced immune function associated with smoking [11].

The optimal timing and intensity of smoking cessation before surgery to reduce postoperative pulmonary complications remain unclear, but the period before a planned surgery might still be seen as a window of opportunity for smoking interventions [8,10,12]. A multicenter randomized control trial where smoking cessation was instituted after operation for acute fracture showed a decreased risk of postoperative complications in the intervention group, indicating that even cessation after surgery can be beneficial [13]. In contrast, findings reported in a Cochrane review [10], based on indirect comparisons and evidence from two small trials, showed that interventions beginning 4-8 weeks before surgery and including weekly counseling were most likely to have a significant impact on complications and long-term smoking cessation.

### Previous Research and Findings

Over the past few years, it has become more evident that short message service (SMS)–based interventions can help individuals quit smoking. In a Cochrane review from 2016 [14], it was indicated that long-term quit rates increased by 67% among those who were given access to SMS-based smoking-cessation interventions compared to those who were not. These findings were supported by a second meta-analysis conducted the same year, which found that abstinence increased by 63% with the use of SMS-based interventions [15].

Our research group has previously investigated the use of an SMS-based intervention (NEXit) for smoking cessation among university students in Sweden [16-18]. The intervention was evaluated using a two-arm, parallel-group randomized controlled trial including 1590 participants between the ages of 21 and 30 years. With respect to 8-week prolonged abstinence, a statistically significant difference was found between the intervention group (25.9%) and control group (14.6%). Differences in the 4-week point prevalence between the groups were also statistically significant (20.6% versus 14.2%). The intervention has now been adapted to a younger age group and is currently in trial among high-school students in Sweden [19].

There is, however, no research in Sweden or elsewhere on the use of SMS-based interventions for smoking cessation prior to surgery. Given the success of the approach in other contexts and the importance of smoking cessation prior to surgery, it is valuable to determine if such an approach could work in this context.

### Aims and Hypotheses

There is strong evidence that short-term smoking cessation before surgery can reduce postoperative complications and morbidity. There are, however, several structural problems in the Swedish health care system concerning the organization of smoking cessation for patients waiting for surgery. The overall aim of this project is to fill the knowledge gap on whether an SMS-based smoking-cessation intervention can be effective in helping patients stop smoking preoperatively. This trial protocol includes a two-arm parallel-group randomized controlled trial that aims to evaluate the effectiveness of the SMS-based intervention on smoking behavior as a tool in addition to the current routine treatment and to measure potential mediators of the intervention on smoking cessation.

There are two hypotheses in this study: (1) Smoking outcome measures will differ between the two groups at 3, 6, and 12 months after randomization. The 3-month period will be the primary time point. (2) Importance of smoking cessation and self-efficacy will mediate the effects of the intervention on smoking outcomes at 3 months. The same measures at 3 months will mediate the effect of the intervention at 6 months (and 6 months on 12 months).

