#### Follow-Up

Six weeks after randomization, mediating factors will be assessed through a questionnaire. At 3, 6, and 12 months after randomization, smoking-cessation outcomes and mediating factors will be assessed through questionnaires. In all cases, hyperlinks to the questionnaires will be sent to participants’ mobile phones via an SMS. Two reminders will be sent, after which phone calls will be made to collect the primary outcome measures only. A maximum of five phone calls will be made to each participant at each follow-up stage.

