#### Measures

All questions asked at baseline and subsequent follow-ups can be found in Multimedia Appendix 1.

Hypothesis 1:

Primary outcome measures: Prolonged abstinence and point prevalence of smoking abstinence.Secondary outcome measures: Seven-day point prevalence of smoking abstinence, mean number of quit attempts since participation in the trial, number of uses of other smoking-cessation services since joining the trial, and number of cigarettes smoked weekly (if still smoking).

Hypothesis 2:

Mediation measures: Importance and self-efficacy of quitting and staying smoke free.

Prolonged abstinence is defined according to the Russell standard definition [38], applying the usual threshold of not smoking more than 5 cigarettes in the past 8 weeks (thus allowing for a 4-week grace period). The 8-week period is then adjusted to 5 and 11 months at 6- and 12-months of follow-up, respectively. Point prevalence of smoking abstinence is defined as not smoking any cigarette in the past 4 weeks, which aims to capture delayed effects of the intervention, as suggested by the Society for Research on Nicotine and Tobacco [39]. Importance and self-efficacy will be investigated by two questions (Multimedia Appendix 1) rated on a scale of 1 to 10.

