For all models, coefficients of interest will be assessed for statistical significance using a null hypothesis testing approach, where tests will be two-tailed at the .05 significance level with 95% CIs. Alongside the null hypothesis tests, posterior distributions using a Bayesian approach will be calculated for each coefficient [41]. Both significance tests and posterior distributions will create a basis for scientific inference.

#### Hypothesis 2

Mediators will be explored using a causal inference framework [42], where Monte Carlo methods are relied upon for inference. This allows for any type of model (linear and nonlinear) to be used to represent the relationships between the group allocation, mediating variable, and the outcome. Three models will be created for each outcome measure, two of which investigate the mediating factors on their own and a third that incorporates both mediators at once. If any baseline characteristics are found to moderate the effect in the primary analysis, additional mediator models will be created to include these characteristics as moderators.

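### For prolonged abstinence, the mediators are measured after the outcome window has opened, so the planned models cannot separate mediation from the effect of smoking status on the ratings

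*Protocol article*

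**What the plan says.** The Aims and Hypotheses section states the mediation hypothesis for the primary time point, "Importance of smoking cessation and self-efficacy will mediate the effects of the intervention on smoking outcomes at 3 months", and extends it to later visits: "The same measures at 3 months will mediate the effect of the intervention at 6 months (and 6 months on 12 months").

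The Follow-Up section gives the schedule: "Six weeks after randomization, mediating factors will be assessed through a questionnaire", and mediators are assessed again with the smoking outcomes at 3, 6 and 12 months.

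The Measures section defines prolonged abstinence at 3 months by "applying the usual threshold of not smoking more than 5 cigarettes in the past 8 weeks (thus allowing for a 4-week grace period"), and then says "The 8-week period is then adjusted to 5 and 11 months at 6- and 12-months of follow-up, respectively". The other primary outcome has a short window: "Point prevalence of smoking abstinence is defined as not smoking any cigarette in the past 4 weeks".

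Under Statistical Analysis, Hypothesis 2, the article says "Mediators will be explored using a causal inference framework" and "Three models will be created for each outcome measure". Prolonged abstinence is not excepted. Nothing in the article mentions that the mediator visit falls inside this outcome's window, or that smoking status at that visit will be taken into account.

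**The concern.** A causal mediation model needs the mediator to come before the outcome. Prolonged abstinence is a record of what happened over a stretch of time, and a participant fails it once the cigarette threshold is passed. If the rating is taken part-way through that stretch, some participants have already failed. For them the rating cannot have caused the failure. An association must come from failure affecting the rating, or from a cause common to both.

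It is plausible that people who have stopped smoking feel more able to stay stopped, and that people who have relapsed feel less able. If the intervention makes early quitting more common, ratings would then differ between arms and would also track the outcome. That is the pattern a mediation model reads as an indirect effect. At stake is what can be concluded from hypothesis 2, one of the trial's two stated hypotheses. The treatment comparison under hypothesis 1 is not touched.

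**Working it through.** **Inputs from the article.** Mediator visits: week 6 and months 3, 6 and 12 (Follow-Up). Pairings: month 3 with the 6-month outcome, month 6 with the 12-month outcome (Aims and Hypotheses). For the 3-month outcome, week 6 is the only earlier post-baseline rating, so that pairing is inferred. Look-back for prolonged abstinence: 8 weeks, 5 months, 11 months; for point prevalence: 4 weeks (Measures).

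**Step 1, the plan's own figure.** Window opening = follow-up time − look-back. With 3 months taken as 12 weeks, 12 − 8 = week 4, which reproduces the stated 4-week grace period. With calendar months (52.1775/12 = 4.348 weeks each), 3 months = 13.04 weeks and the window opens at 13.04 − 8 = week 5.04.

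**Step 2, lag of the mediator after opening.** Lag = mediator time − window opening.

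| Prolonged abstinence | Window opens | Mediator | Lag | Share of window elapsed |
|---|---|---|---|---|
| 3 months, 12-week reading | week 4 | week 6 | 2 weeks | 2/8 = 25% |
| 3 months, calendar reading | week 5.04 | week 6 | 0.96 weeks | 0.96/8 = 12% |
| 6 months | 6 − 5 = month 1 | month 3 | 2 months | 2/5 = 40% |
| 12 months | 12 − 11 = month 1 | month 6 | 5 months | 5/11 = 45% |

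**Step 3, how many outcomes are already fixed.** The 3-month window (about weeks 4-5 to 12-13) lies essentially inside the 6-month window (months 1 to 6). Only the length of the period is said to change, so I take the 5-cigarette threshold as unchanged; a failure at 3 months is then also a failure at 6 months. The Power Calculation section gives 8-week abstinence of 25.9% and 14.6% in the earlier student trial. If those rates held here, 100 − 25.9 = 74.1% of the intervention arm and 100 − 14.6 = 85.4% of controls would already have failed the 6-month outcome when rating the mediators at month 3. At month 6 the share already failed for the 12-month outcome would be at least as large. For week 6 the article gives no figure.

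**Step 4, point prevalence for comparison.** Its window opens at week 12 − 4 = 8 or 13.04 − 4 = 9.04, at month 6 − 4/4.348 = 5.08, and at month 12 − 4/4.348 = 11.08. The mediator precedes it by 2 to 3 weeks, 2.1 months and 5.1 months. The order is right.

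**Step 5, is right order enough? An illustration.** Assumptions, none from the article: 37% and 21% abstinent at week 6; 70% of these stay abstinent (0.37 × 0.70 = 25.9%, 0.21 × 0.70 = 14.7%, chosen to match the planning rates); rating SD 2; no effect of the rating on the outcome; abstinence at week 6 raises the rating by 1, 2 or 3 points. In large simulated samples the apparent proportion mediated was:

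| Shift in rating | Prolonged abstinence | 4-week point prevalence |
|---|---|---|
| 1 point | about 6% | about 5-6% |
| 2 points | about 19% | about 18-19% |
| 3 points | about 33% | about 33% |

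The truth is 0% throughout. Repeat runs move the levels by a few percentage points, but the two outcomes stay nearly equal. Adjusting for abstinence at the mediator visit brought the figure to 0%. These numbers illustrate confounding by smoking status at the mediator visit. They do not measure the effect of window overlap.

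**The case against.** The strongest reply has four parts.

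First, the Discussion already calls the mediation analyses preliminary and exploratory. That stands, and it lowers the consequence. It does not correct the order, and the Hypothesis 2 section still claims a causal framework.

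Second, at 3 months the pairing with week 6 is inferred and the overlap is only 1-2 weeks of 8. That stands too; the case rests mainly on the 6- and 12-month models, whose pairings are explicit.

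Third, moving to point prevalence does not cure the bias, as step 5 shows. This is correct and shapes the fix: smoking status at the mediator visit has to be dealt with at 3 months as well as later.

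Fourth, a reader might infer that hypothesis 2 would appear supported whether or not it is true. The documents do not support that. How far quitting moves a rating on the 1-10 scale is unknown. With 384 analysed, no true mediation, SD 2, and 50-90% of eventual failures already failed at the rating, the interval for the indirect effect excluded zero in 0-6%, 9-11% and 8-30% of simulated trials for shifts of 1, 2 and 3 points. With the step 5 inputs it did so in 9%, 26% and 53%. A false finding is possible and, with a large shift, fairly likely; it is not assured.

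Adjustment for baseline importance and self-efficacy may already be planned: the Hypothesis 1 section lists both as covariates for all models. Whether that reaches the mediation models is unclear, and it would not address the overlap.

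**Conclusion.** The point holds for prolonged abstinence. On the article's own definitions the mediators are rated about 1-2 weeks, 2 months and 5 months after the outcome window opens, with 12-25%, 40% and 45% of the window gone. Any effect of smoking status on the ratings would be counted as mediation and could not be separated from it. The direction of bias is towards apparent mediation if quitting raises the ratings; its size cannot be derived from the documents. The lags rest on the stated windows and schedule plus the inferred week-6 pairing. The 74% and 85% with fixed outcomes rest on the student-trial rates carrying over. It would be wrong to conclude that window overlap by itself produces the percentages in step 5, or that point prevalence is free of the problem. This should be corrected before analysis, but it bears on an exploratory analysis and not on the primary treatment comparison.

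**What to change.** 1. Make no causal mediation claim for prolonged abstinence. Drop those models, or report them as associational and say why.
2. Base causal mediation on 4-week point prevalence, with 7-day point prevalence alongside, since their windows start after the mediator visit.
3. State that smoking status at the mediator visit is a post-treatment confounder at 3, 6 and 12 months. For the 6- and 12-month models it is collected at the mediator visit (months 3 and 6), so use a mediation method that allows for it. For the 3-month model, the article lists only mediators at week 6; unless the questionnaire, which is not shown, also records smoking then, report the result as associational or with a sensitivity analysis for mediator-outcome confounding.
4. State which mediator visit serves the 3-month outcome, and confirm that the baseline importance and self-efficacy covariates apply to the mediation models.

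The cost is wording in the analysis plan and a weaker, exploratory mediation statement for one of the two primary outcomes. No new data are required.

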## Methods

### Intervention Content

#### Rationale

Previous cessation interventions have not been able to establish clear evidence of which components or techniques are most essential to include for smoking cessation [20-22]. In the absence of a clear theory as the basis of the intervention, the content of the text messages in the proposed intervention was based on our previous smoking-cessation research concerning university students, key elements from other internet- and SMS-based interventions, official manuals about smoking cessation, and books from cessation experts [14,16-18,23-32]. The length of the intervention of 12 weeks was set to conform with previous interventions, recommendations, and our own previous experience [23,26,28,31-37].

The messages were developed with the intention to encourage participants to quit smoking. The messages included information about the consequences of smoking, how to quit and stay smoke free, tasks to perform (such as getting rid of ashtrays and cigarettes), coping strategies to deal with cravings, motivational messages, and how to avoid smoking triggers. Content that specifically focused on the benefits of smoking cessation prior to the trial was added. One of the initial messages also contains a hyperlink to a video where a surgeon gives a motivational speech and explains why it is important to quit smoking prior to surgery.

#### Intervention

The proposed intervention consists of 130 messages that are sent via SMS to the participant’s mobile phone over a 12-week period. Two to four messages will be sent per day during the first few weeks, which will be reduced to two per day during the middle part of the intervention and further reduced to one message per day during the latter part of the intervention. Some of the messages include hyperlinks that take the participants to interactive modules that they should engage with. There are a total of nine such modules, and throughout the intervention period, participants will be reminded of their responses to modules they have completed in the past.

Briefly, the nine interactive modules that users engage with throughout the intervention are as follows:

A set of tips and tasks, of which participants choose five that suit them.A set of reasons to quit smoking, of which the participants choose five (or enter their own reason).A series of questions that result in a plan for how to deal with certain situations in which the temptation to smoke is increased, such as “When I have had my dinner, I will have a piece of fruit” or “While I am waiting for the bus, I will listen to music.”A set of information boxes that relate to withdrawal symptoms.A set of tips that participants choose, or enter on their own, on what to do when craving cigarettes.A set of information boxes with information about what happens to the human body after smoking cessation.A set of information boxes with information about good habits that can replace the smoking habit.A series of questions that lead to suggestions of physical activities that the participant might want to try in order to improve his/her health further and relieve abstinence.A pros and cons list created by the participant for smoking cessation.

In summary, the intervention is based on previous research and expert knowledge and has been designed to suit the specific context of the current situation of the participant—a situation in which they must quit smoking preoperatively.

